#### Sample size considerations

The ITS analysis will include monthly data aggregated from 94 hospitals over 5 years (60 time points total). Recommendations are to include between 40 and 50 observations for robust statistical analysis of ITS designs [32]; moreover, to avoid over-fitting of segmented regression models, at least 10 observations for each regression coefficient is required [33]. With 4 regression coefficients in our planned analyses, 60 time points is adequate. Furthermore, to help ensure stability of the monthly proportions, it is recommended that measurements be based on at least 100 observations at each time point. After pooling across all hospitals (approximately 12,000 births per month), the minimum monthly denominator will range from approximately 200 (repeat Caesarian section) to 7800 (group B Streptococcus screening). Thus, we expect to have sufficient sample sizes to ensure stable estimates.

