### Objective 4—to identify factors significantly associated with differences in hospital performance before and after implementation of the MND

#### Analysis

We will conduct a multivariable generalized linear mixed-effects regression analysis of the repeated indicators at each hospital to identify those factors that are most predictive of between-hospital differences in effectiveness of the MND. Unlike the pooled analysis for objective 1, this analysis will use individual hospital-level data. The analysis will be limited to hospitals with annual birth volumes >100 to avoid numerical instability due to small denominators. With an anticipated 60 % response rate for the survey, approximately 50 hospitals will be included in the analysis. Appropriate time intervals for these longitudinal analyses will be chosen to avoid instability due to low denominators: we anticipate that 4 KPIs will be analyzed using quarterly intervals (12 pre-implementation and 8 post-implementation time points) and 2 KPIs will be analyzed using annual intervals (3 pre-implementation and 2 post-implementation time points). The generalized linear mixed-effects regression analysis of the repeated proportions at each hospital will use either a log-link function with the denominator specified as an offset term or a logit link function with the outcome specified in binomial form. For quarterly measurements, time will be modeled using a semi-parametric spline function with knots separating the pre- and post-implementation phases. Random intercepts and slopes will be specified for each hospital, and hospital-specific trends will be estimated using empirical Bayes’ best linear unbiased predictors. An advantage of this model is that estimates can be obtained even for smaller hospitals, as these estimates “borrow information” from the rest of the data, resulting in individual means that are shrunken towards the population mean. For annual measurements, time will be analyzed as a categorical variable and random intercepts will be specified for each hospital. To identify factors associated with differences among hospital trends over time, the candidate predictor variables identified in the survey related to the attributes of the MND (e.g., clarity of the KPI definitions, evidence summaries, visual displays, and audit features), contextual factors (e.g., leadership, culture, formal and informal interactions, and resources), and facilitation factors (e.g., training, resources, internal and external supports) will be entered into the model, together with their product interaction terms with time. To reduce the potential number of coefficients (2 intercepts and 2 slopes, 18–20 candidate predictors, 54–60 interaction terms), we will enter each candidate predictor variable plus its interactions with time separately into the model. Only those factors that have significant main or interaction effects will be considered for the full multivariable model. To arrive at a more parsimonious final model, we will use stepwise backward elimination, first removing interaction terms as necessary and then main effects.

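### Objective 4 lets a hospital factor enter and stay in the model on a pre-existing level difference, and its screening and backward elimination in about 50 hospitals will also let chance factors through

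*Protocol article*

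**What the plan says.** The Analysis section of Objective 4 sets out the whole selection procedure.

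- **Aim.** To find the factors that best predict how the effect of the dashboard, and the trend over time, differs between hospitals.
- **Sample.** "With an anticipated 60 % response rate for the survey, approximately 50 hospitals will be included in the analysis". Hospitals with 100 or fewer births a year are left out.
- **Candidates.** The model terms are counted as "2 intercepts and 2 slopes, 18–20 candidate predictors, 54–60 interaction terms".
- **Screen.** Each factor is entered on its own with its time interactions. Then: "Only those factors that have significant main or interaction effects will be considered for the full multivariable model".
- **Reduction.** "we will use stepwise backward elimination, first removing interaction terms as necessary and then main effects".
- **Repetition.** The procedure covers six indicators, four of them quarterly ("we anticipate that 4 KPIs will be analyzed using quarterly intervals (12 pre-implementation and 8 post-implementation time points") and two annual.

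The section gives no significance level for either step. It does not say whether a significant interaction means any single term or a joint test.

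**The concern.** The aim concerns a change after implementation, but the entry criterion also accepts evidence about something else. In a model with time interactions, the main effect of a factor is a difference in level at the time origin. Hospitals with strong leadership, for example, might already have had lower episiotomy rates in 2009. That would admit leadership to the model even if such hospitals responded to the dashboard exactly as the others did. The elimination step does not correct this. It takes out interactions first, so a factor can lose every interaction and remain on its main effect.

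The second issue is chance. Each factor has several ways to pass, there are 18–20 factors and six indicators, and the factors carry information only between hospitals.

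According to the Discussion, the findings are meant to point to the organizational and facilitation factors that matter and to support later cluster randomized trials. A factor selected on a baseline difference or by chance would be a poor basis for either.

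**Working it through.** **1. The plan's own count.** Three time interactions per factor give 3 × 18 = 54 and 3 × 20 = 60, as stated. With 2 intercepts and 2 slopes the candidate set is 4 + 18 + 54 = 76 to 4 + 20 + 60 = 84 coefficients. Each factor therefore has four terms: one main effect and three interactions.

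**2. What the four terms mean.** The article does not give the coding of time. Under the usual segmented coding they are:

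| Term | Describes |
|---|---|
| Factor (main effect) | difference in initial level, before the dashboard |
| Factor × pre-implementation slope | difference in trend before the dashboard |
| Factor × level change | difference in immediate response |
| Factor × slope change | difference in later response |

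Only the last two bear on effectiveness. With another time origin, the main effect is still a difference in level at one time point, not a difference in change.

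**3. Number of independent units.** 94 × 0.60 = 56.4 before the volume restriction. About 50 respondents implies 50 / 0.60 ≈ 83 eligible hospitals, which is plausible, but the number excluded is not given. A survey factor has one value per hospital, so repeated quarters add little information about it.

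**4. Null factors passing the screen, per quarterly indicator.** The significance level is an assumption.

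- Any of four independent terms at 0.05: 1 − 0.95⁴ = 0.1855. Then 18 × 0.1855 = 3.3 and 20 × 0.1855 = 3.7.
- One joint test per factor at 0.05: 18 × 0.05 = 0.9 and 20 × 0.05 = 1.0.
- Any of four terms, 20 factors, other levels: 0.8 at 0.01, 6.9 at 0.10, 11.8 at 0.20.

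Annual indicators with five-level categorical time have four interactions, hence five terms: 1 − 0.95⁵ = 0.2262, or 4.1–4.5 null factors.

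**5. How many of these pass on pre-implementation terms alone.** With independent terms at 0.05: (1 − 0.95²) × 0.95² = 0.0975 × 0.9025 = 0.0880. That is 18 × 0.0880 = 1.6 to 20 × 0.0880 = 1.8 factors, or 0.0880 / 0.1855 = 47% of chance admissions.

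**6. Does backward elimination remove them?** This was simulated in simplified form: 50 hospitals, 20 quarterly points, 20 factors, Gaussian outcomes, regression of hospital-specific segmented coefficients on the factors, 0.05 at both steps, 600 runs, assumed variance components.

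- All factors null and uncorrelated: 3.6 admitted per indicator, 1.6 of them with no significant level-change or slope-change term. 3.0 remained in the final model, and 99% of runs kept at least one.
- All null, correlation 0.3 between factors: 3.4 admitted, 2.2 remained, and 95% of runs kept at least one.
- With some true factors, the false share of retained factors was as follows (effects in SD of the estimated level change):

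| True factors | Effect | False share |
|---|---|---|
| 2 | 0.3 | 70% |
| 5 | 0.3 | 48% |
| 5 | 0.5 | 36% |
| 8 | 0.4 | 30% |
| 10 | 0.3 | 29% |

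**7. Exaggeration.** In a simple regression over 50 hospitals, a two-sided test at 0.05 needs t ≈ 2.01 on 48 degrees of freedom. This corresponds to |r| = 2.01 / √(2.01² + 48) = 0.28. A factor that passes such a test must show at least this correlation in the sample, however weak its true relation.

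**The case against.** The strongest reply is that the plan is more cautious than the charge suggests. The abstract words objective 4 broadly, as predicting differences in hospital performance, which could include differences in level. The coding of time is not given. A factor kept only as a main effect would be visible as such, and nothing says it would be reported as modifying the dashboard's effect. The candidates come from a framework, interviews and a readiness instrument, so a world in which all are null is a worst case. All this is fair. But the Analysis section itself states the narrower aim, and a level difference at one time point is not a before-to-after difference, which is what the heading of Objective 4 names.

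Four stronger readings are tempting and are not supported.

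- **That the plan breaks its own rule of ten.** The rule, "at least 10 observations for each regression coefficient is required", stands under Objective 1, is set for segmented regression and counts observations. It is met there, at 60 / 4 = 15. Counted in records, the quarterly indicators have 50 × 20 = 1000, or 1000 / 84 = 11.9 to 1000 / 76 = 13.2 per coefficient even for the full set. The annual indicators fall short (250 / 84 = 3.0 to 250 / 76 = 3.3), but only for a full set that the plan screens in order to avoid. Counting hospitals is a sound statistical argument, but it is not a contradiction in the document.
- **That most selected factors will be chance.** This depends on the unstated significance level, the form of the test and the number of true factors. The simulated false share ran from 29% to 100%.
- **That intervals are reported as if the model had been fixed in advance.** No P value or interval reporting is stated for Objective 4. The 95% intervals belong to Objective 1.
- **That adjustment for level of care, birth volume or baseline performance is missing.** Covariate lists may be left to the analysis plan. Forcing three such three-category variables with their time interactions would add 6 + 18 = 24 coefficients, and a baseline performance zone would be computed from outcomes that the model already contains.

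**Conclusion.** The point holds in two parts. The mismatch between aim and criterion rests on the text and on usual segmented coding, and needs no assumption about the significance level: a factor can be selected without any evidence that it relates to the dashboard's effect. The chance part is conditional. At an assumed 0.05, about 1 null factor per indicator passes with a joint test and 3 to 4 with any of four independent terms. In the simulation, backward elimination left most of them in the model. A substantial share of the named factors could be chance findings with overstated effects. How large a share cannot be fixed from the documents. The matter should be corrected before the Objective 4 analysis, but it does not touch Objectives 1 to 3.

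**What to change.** 1. Admit and retain each factor on a single joint test of its post-implementation interaction terms: level change and slope change for quarterly indicators, factor × post for annual ones. Keep the main effect and the pre-implementation slope interaction as adjustment terms that cannot qualify a factor.
2. State the significance level and the coding of time.
3. Control the false discovery rate, for example by Benjamini-Hochberg, over factors and indicators (18 × 6 = 108 to 20 × 6 = 120 tests). Alternatively, label the selected factors as hypothesis-generating.
4. Optionally, replace backward elimination by a penalised fit tuned by cross-validation with hospitals as folds.

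The joint test alone limits chance admissions at 0.05 to 0.9–1.0 per indicator and removes those that rest only on pre-implementation terms. No new data are needed. The cost is a change of wording and fewer individual factors that can be claimed.

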
### Study status

At the time of preparing this manuscript, we have hired research staff, obtained ethical approval, developed tools to classify hospitals, developed and piloted data collection tools, and begun the process of data collection for the ITS and provincial survey.

## Discussion

### Strengths and limitations

A major strength of our study is the use of a mixed methods approach to obtain more in-depth understanding of factors that influence use of an A&F system to improve performance. Additional strengths include the use of a theoretical framework (PARiHS) and a validated instrument (OR4KT) to guide data collection and analysis for objectives 2 (interviews) and 3 (provincial survey). We will have a large and inclusive sample size—all 94 maternal-newborn hospitals in Ontario for objectives 1 (ITS) and 3 (provincial survey), and therefore, we have the unique opportunity to see a wide variety of practice patterns and to examine use of the MND at a health system level, across diverse organizations and levels of care. We anticipate our project will provide important information to health-care funders and legislators, hospital administrators, and health-care providers. We will also use the findings from this collection of studies to support the development of a series of cluster randomized trials to test how to best to implement A&F in the future.

Study limitations include (1) exclusion of home births as the MND was customized for hospital birth performance issues; however, this group accounts for less than 2 % of all births in the province. Hospital births by midwives will be included; (2) any observed performance change could be due to factors other than the MND implementation; however, we will implement several strategies to allow us to quantitatively assess whether this may be the case; (3) a small number of hospitals will be excluded from the multivariable regression analysis due to low birth volumes; however, all remaining hospitals will be included in multivariable regression analyses to identify predictor variables; and (4) there is a risk of non-response bias in the provincial survey; however, BORN Ontario works within a network of all maternal-newborn care organizations in the province and has a well-established communication network established with health-care providers working within these settings, which will facilitate recruitment and data collection.

### Relevance, impact, and urgency of this study

Wide variation in maternal-newborn care practices and outcomes across Ontario indicates that optimal care is not always delivered [1]. BORN Ontario has developed a unique online A&F system in Canada to facilitate uptake of evidence to practice on a large scale. Although a number of characteristics of organizational readiness for change have been reported [51, 52] (e.g., leadership, resources, situational factors, culture and values, policies and procedures), we have the opportunity to augment this knowledge base and determine to what extent organizations with an effective data capture system vary in their readiness and capability to undertake change for enhancing quality care. This study will explore factors that influence effective use of an electronic A&F system and how organizations respond when warning signals occur. Since the protocol was developed, additional evidence [8] has been published emphasizing the need for further research on A&F. The MND provides us with a unique environment for knowledge translation science and the opportunity to study A&F within the context of a large population of maternal-newborn care providers, births, and hospitals with different levels of care and birth volumes. This will increase our understanding about what makes A&F more or less effective and what contextual and facilitation factors are most important for successful implementation of the MND to improve practice.

If this study demonstrates increased use and effectiveness of the MND to improve practice related to some or all of the KPIs, we anticipate several opportunities to improve on its design as well as to identify key organizational and facilitation factors predictive of increased use of an A&F system. This information will help to increase understanding about when, for whom, in what way and why A&F works in some settings and not others. First, it could provide information to improve the design features for A&F systems targeting organization level indicators (e.g., different data tables, graphs to display comparator data or trends over time, custom query features to allow sites to tailor displays to suit their organizational needs). Second, it could help to identify the most important factors that influence organizations’ readiness for change and resources that could be developed to support change related to various KPIs. Third, it could increase awareness about key issues to consider when selecting indicators to target provincial level quality improvement initiatives. Providing local experts with the tools to identify evidence-practice gaps, initiate practice change, and tailor strategies to effectively counter the barriers identified may improve the uptake of best evidence and the sustainability of practice change. This study addresses some of the evidence gaps found in the literature about A&F and as a naturalistic study embedded within a provincial context of maternal-newborn care, we have the potential to improve knowledge about the effectiveness of A&F to improve care. We have a wealth of data available in the BIS and a mandate to use that data to facilitate care where possible. The use of A&F to increase health-care provider awareness about evidence-practice gaps and to trigger quality improvement initiatives is the first step to improve care and ultimately patient outcomes.

## Ethics approval and consent to participate

The Children’s Hospital of Eastern Ontario Research Ethics Board (REB) has reviewed and approved this study (protocol #13/218X). In addition, REB approval has been received from the University of Ottawa (A01-14-03). Informed consent will be obtained from all participants. All data collection and reporting will be compliant with the Canadian privacy laws and Ontario PHIPA legislation regulating the use of BORN Ontario Registry data. Data will be securely stored at the BORN Ontario offices, Centre for Practice Changing Research Building, [name], Children’s Hospital of Eastern Ontario, Ottawa, Ontario. All study records and documents will be stored for 7 years after the study has ended.

### Consent for publication

Not applicable.

### Availability of data and material

The research described here is being conducted at Better Outcomes Registry & Network (BORN) Ontario, a provincial maternal-child registry. BORN Ontario holds copies of province-wide databases that contain personal health information, and the record-level data cannot be publicly shared, according to the privacy laws in Ontario. Access to aggregated de-identified data on which the conclusions rely will be available, on request, from BORN Ontario. For future publications reporting results, aggregated data tables will be provided as supplementary files where possible.

## Abbreviations

A&F: audit and feedback
BIS: BORN Information System
BORN: Better Outcomes Registry & Network Ontario
CIHR: Canadian Institutes of Health Research
ITS: interrupted time series
KPI: key performance indicator
MND: maternal-newborn dashboard
OR4KT: Organization Readiness for Knowledge Translation
PARiHS: Promoting Action on Research Implementation in Health Services
PHIPA: Personal Health Information Protection Act
